### Instruments

Four types of data are being collected: (1) intervention implementation outcomes (to assess feasibility); (2) adolescents’ outcomes (to assess sensitivity to change), including self-report instruments, physiological measures and neuropsychological tasks; (3) caregiver outcomes (all self-reported instruments, to assess sensitivity to change); and (4) costs (to assess feasibility). All self-reported instruments and neuropsychological tasks included in the assessment have been adapted in each site as part of the ALIVE project. These are described in more detail below and reported in Tables 5 and 6. Unless otherwise stated, all adolescent and caregiver outcomes are assessed at all timepoints. Full adolescent and caregiver assessments are also available in supplementary files 3 and 4.

**Table 5 Tab5:** Overview of self-report adolescent instruments

Name	Domain	Construct	# Items	Responses/Scoring	Country/Regional Psychometrics	Time (minutes)
Demographics	Demographics	Age, gender, ethnicity, etc	17	Multiple response options; used as individual item covariates in analyses	Not applicable	2
Education (Risk score items: [36]) - Schooling	Education	Educational status, disruptions	16	Multiple options; used as individual item covariates in analyses; items contribute to calculation of IDEA Risk Score	Not applicable for individual items; IDEA-RS c-statistic described below	2
Measurement of Mental Health among Adolescents and Young People at the Population Level (MMAPP) [37]	Mental health	Anxiety, depression	28	Frequency of symptoms (4 options, 0 never to 3 always); Total PHQ-A and GAD-7 score; depression caseness (score > = 16 (South Africa), > = 15 (Nepal), > = 14 (Colombia)); anxiety caseness (score > = 12 (Colombia and South Africa), > = 10 (Nepal))^A^	Depression: Colombia (≥ 14): 0.72 (sens); 0.74 (spec) Nepal (≥ 15): 0.88 (sens); 0.83 (spec) SA (≥ 16): 0.75 (sens); 0.79 (spec) Anxiety: Colombia (≥ 12): 0.71 (sens); 0.76 (spec) Nepal (≥ 10): 0.58 (sens); 0.64 (spec) SA (≥ 12): 0.69 (sens); 0.73 (spec)	6
Disruptive Behaviour International Scale (DBIS) [38]	Mental Health	Oppositional defiant disorder, conduct disorder	8	Frequency of symptoms (4 options, 0 never to 3 always); Total disruptive behaviour symptom score (sum of all items)	Nepal only: Cronbach’s *α*: 0.84; test–retest reliability (intraclass correlation 0.93, *r* =.93) [38].	1

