IDEA Risk Score (IDEA-RS) [36]^B^	Risk factors for development of depression	Quality of relationships, substance use, maltreatment	21	Yes/no responses for most questions; To calculate IDEA-RS, 11 items are summed (drawn from this section in addition to demographics and education)	AUC = 0.83 (Nepal; [36]), 0.69 [39], 0.66 (Nigeria; [40])	3
Difficulties in Emotion Regulation Scale (DERS) [41]	Emotion regulation	Awareness of and behavioural response to distress	15	Frequency (0 Never to 4 Always); sum score with reverse coding for select items	Cronbach’s α (Nepal 36-item version with adolescents) = 0.77 [42]	3
Children’s Hope Scale (CHS) [43]	Hope	Agency and pathways hope	6	Frequency (0 Never to 4 Always); Sum score for hope (agency subscore, pathways subscore)	Nepal: Cronbach’s *α* = 71 for agency and.78 for pathways, and test–retest *r* =.70; Metric and scalar invariance are not supported in Nepal (including notable gender differences) [44]; South Africa: English and Afrikaans versions—Cronbach’s α 0.73–0.82, with demonstrated scalar invariance [45]	1
Economic - Expectation and aspirations [46] - Knowledge about education - Financial literacy [47] - Negotiation skills [22]	Economic	Economic decision making, spending, and earning expectations	43	Various response options (e.g. categories for earning expectations; yes/no questions; and level of difficulty questions);		6
Client Service Receipt Inventory, adapted version [48]^C^	Cost consequences	Resource use	8	Response options (vary by question): Yes/No; number of/duration of visits; how much paid)		10
Child and Youth Resilience Measure (CYRM) (Nepal only) [49]	Resilience	Importance of education, food availability, feeling safe, social support	17	Amount (e.g. amount of food) or degree (e.g. how much people like spending time with the adolescent); scoring 1 = Not at all; 5 = A lot	Cronbach’s *α*: 0.84 (based on data from ALIVE survey)	2
Rugged Resilience Measure (RRM) [50] (Nepal only)	Resilience	Controlling emotions, responding to challenges, coping	10	Amount (1 = Not at all; 5 = A lot)	Cronbach’s α: 0.82 (based on data from ALIVE survey)	1

^A^Exact cut-offs for South Africa and Colombia were established after clinical validation study as part of ALIVE

^B^Not assessed at T0

^C^Only assessed at T2

**Table 6 Tab6:** Overview of caregiver self-report instruments

Name	Domain	Construct	# Items	Responses/Scoring	Country/Regional Psychometrics	Time (minutes)

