### Procedures

#### Data collection for pilot cRCT

Refer to Fig. 1 for the SPIRIT schedule of enrolment, interventions and assessments. Adolescents and caregivers will be assessed on four occasions to assess sensitivity to change of measures and to assess a change in incidence of depression and/or anxiety, as well as all other outcomes, from baseline (T0) to post intervention (T1), 12 months post-baseline (T2), and 18 months post-baseline (T3). Baseline data collection for adolescents was ideally completed 1–4 weeks before the intervention started and initiated immediately after the screening questionnaire (MMAPP) and enrolment. If baseline data for caregivers were not already collected as part of the Phase 1 cross-sectional survey, baseline data were also collected 1–4 weeks before the intervention started. Data collection for both adolescents and caregivers at T1, T2 and T3 will be conducted within a 3-week window from the scheduled post-baseline timepoint. Please refer to Fig. 2 for an overview of the timeline for step 1 and step 2 enrolment, interventions and assessments of participants.

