Following multiple imputation of missing data among participants followed-up, models will each be estimated two times for each outcome in each country. First, following an intent-to-treat principle, we will estimate models including all study participants at all timepoints and according to their randomisation allocation, regardless of attendance. Second, the same models will be estimated but only among the subset of adolescent participants who attended > 70% of the 20 intervention sessions (defined as “completers”). Where possible, models will control for variables included in the random selection of schools (district (Colombia), school size (Nepal) and language (South Africa)). The Benjamini–Hochberg correction will be applied to correct for multiple comparisons.

After analyses are conducted on each of the country-specific data sets, cross-country analyses will be conducted; this may include pooled cross-sectional analyses on the baseline data, or pooled outcome analyses assessing change over time. Models will account for clustering at school level, and random intercepts will be specified for schools and participants to reflect the hierarchical structure of the data. To account for the small number of clusters and likely non-normal distribution of outcomes, we will use a Bayesian multilevel negative binomial or Poisson regression model estimated via Markov Chain Monte Carlo. We will conduct heterogeneity analyses to assess differences in the impact of the intervention across sites, employing interaction effects in regression models on a pooled dataset of all three sites. Analyses will be conducted using Stata, version 16.

The abovementioned sensitivity-to-change analyses will provide input for the expected effect sizes that will be needed for sample size calculations for an adequately powered cRCT, if all criteria for progression to full trial are met (see above). For the same purpose, we will use the baseline data to assess the Intracluster Correlation Coefficient (ICC) due to clustering by school. Additionally, because of interest in targeting adolescents most likely to develop depression or anxiety, we will also descriptively review sensitivity to change with stratification by the IDEA-RS. A detailed statistical analyses plan for all outcomes and potential mediation will be developed, and made openly available, before the end of data collection.

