On the one hand, we hypothesise that the self-regulation aspect of the intervention will provide access to a supportive peer group and environment, including caregiver support, as well as a means to build a positive self-concept by independently mastering challenging new tasks, and offer relief from the stress caused by the adversity they experience daily; all of which should promote self-regulation, as well as improve stress management, sleep and communication with caregivers, which in turn may improve hope and increase school attendance and retention, all reducing risk of developing depression or anxiety disorders. We hypothesise that the economic intervention will reduce family financial stress, increase adolescents’ sense of control and security, enhance educational opportunities, increase hope and future orientation, improve peer and family relationships, develop life skills and increase resilience to adverse environments, as well as increase caregivers’ willingness to invest in their children’s human capital and wellbeing, also reducing risk of developing depression or anxiety disorders. It may also increase the set of possible aspirations caregivers have for their children [76], which may in turn lead to larger investments in their human capital. From the adolescent perspective, financial education should empower them to make better informed decisions about the management of their finances, including the cash transfers. Similarly, negotiation training and information on education should enable the adolescents to increase the probability of strategic cooperation that may strengthen their ability to influence their parents’ decision to raise investments. This may improve education outcomes in the short- to medium-term and promote mental wellbeing among adolescents. It is thus essential to conduct a feasibility study first that combines both elements of self-regulation and anti-poverty interventions, as well as assesses the relative change between intervention arms that combine or separate these elements.

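### The review stratified by IDEA-RS is meant to guide targeting, but the score is not taken at baseline and no earlier source is named, so its strata may not reflect pre-intervention risk

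*Protocol article*

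**What the plan says.** Under Sensitivity to change analyses on participants outcome data, the protocol article plans a stratified look at the results: "we will also descriptively review sensitivity to change with stratification by the IDEA-RS". The reason it gives is a wish to inform whom to target, namely those at highest risk of either disorder.

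Under Instruments, the default schedule is this: "Unless otherwise stated, all adolescent and caregiver outcomes are assessed at all timepoints". Table 5 states an exception for this score. Its row is marked with footnote B, which reads "Not assessed at T0". Under Data collection for pilot cRCT, T0 is baseline, T1 is post-intervention, and T2 and T3 are 12 and 18 months after baseline.

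Table 5 gives the construct as "Quality of relationships, substance use, maltreatment". The score sums 11 items taken from that section and from the demographics and education sections. Outcome instruments for adolescents also lists the score among the secondary mental health outcomes.

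**The concern.** Choosing whom a full trial should target requires a risk measure taken before the intervention. If the schedule and the stratification are both followed as written, the score is first measured after the intervention. Two problems follow.

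- **Timing.** Someone already above the cut-off at T1 would have risk and outcome recorded at the same visit. The stratum then cannot show who was likely to become a case.
- **Selection.** If an intervention lowers the score, some adolescents who were high-risk at the start move to the low-risk stratum in that arm but not in control. The strata then hold different kinds of people in different arms.

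At stake is the advice this review gives on whom to enrol next.

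**Working it through.** The article states no figure that depends on this point, so there is none to reproduce. The check sets the statements side by side and then illustrates the possible size.

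**Step 1: when the score is first available.** The default is every timepoint, and footnote B removes T0. The first score in the trial schedule is therefore at T1, post-intervention.

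**Step 2: whether it precedes the outcome.** The cumulative incidence described in the sensitivity-to-change section counts anyone above a cut-off at any follow-up, so T1 counts. A T1 score is concurrent with the first cases. This holds in the control arm too, and it holds even if no intervention moves the score.

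**Step 3: whether the interventions could move it.** The Discussion expects the economic intervention to "improve peer and family relationships, develop life skills and increase resilience to adverse environments". It expects the self-regulation intervention to improve communication with caregivers and to raise school attendance and retention. These overlap with the relationship content of the score, and may overlap with the education items that feed it. Substance use and maltreatment are not named there as aims, and some of the 11 items are demographic. Only part of the score is plausibly open to change, and the article does not say how much.

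**Step 4: whether an earlier source is named.** Participant recruitment describes a Phase 1 survey of about 500 adolescents per site, from which the trial sample was drawn. Its instrument list is not given. Data collection for pilot cRCT allows Phase 1 data to serve as baseline for caregivers and makes no such statement about this score.

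**Step 5: illustrative size.** Every input here is an assumption; none comes from the article.

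- Baseline risk r0 is standard normal, with arms allocated at random.
- Follow-up score: r1 = ρ·r0 + √(1 − ρ²)·noise − d in the treated arm; ρ is 0.5 or 0.7, and d is 0, 0.2 or 0.5 SD.
- Event probability = 1/(1 + exp(1.1 − 0.8·r0)). It depends on baseline risk only, so the true arm effect is nil. Overall incidence is about 27%.
- Strata are split at the pooled median of r1, with 2,000,000 draws per scenario.

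| ρ | d (SD) | High stratum, treated / control | Baseline-risk gap within strata, high / low (SD) | False event difference, high / low (points) |
|---|---|---|---|---|
| 0.5 | 0 | 50% / 50% | about 0 / about 0 | −0.1 / −0.2 |
| 0.5 | 0.2 | 46% / 54% | 0.065 / 0.064 | 1.0 / 0.8 |
| 0.5 | 0.5 | 40% / 60% | 0.157 / 0.159 | 2.7 / 2.2 |
| 0.7 | 0 | 50% / 50% | about 0 / about 0 | −0.1 / 0.0 |
| 0.7 | 0.2 | 46% / 54% | 0.088 / 0.087 | 1.4 / 1.1 |
| 0.7 | 0.5 | 40% / 60% | 0.222 / 0.220 | 3.7 / 2.9 |

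Differences are treated minus control. Wherever the score shifts, the treated arm looks worse in both strata although nothing happened. With strata cut on r0 instead, the differences are at most 0.3 points, which is simulation error.

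**Step 6: against sampling noise.** With the planned 60 per arm per country halved to 30, and 27% incidence, the standard error of an arm difference is √(2 × 0.27 × 0.73 / 30) = 11.5 points. Pooling countries, 628/4 = 157 per arm, about 78 per stratum, gives √(2 × 0.27 × 0.73 / 78) = 7.1 points. Both ignore clustering, which would normally widen them.

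**The case against.** The strongest reply is that a pre-intervention score may exist. The sample came from Phase 1, and Table 5 quotes reliability figures for two resilience scales from ALIVE survey data, so some of these instruments were used in a survey of the project. Footnote B could mean that the score had already been taken. Figures 1 and 2 and the supplementary assessment forms, which might settle this, were not available for this check, and an analysis plan is promised. That reply stands as a condition on the point. It does not remove the point: the article states both the stratifier and its absence at T0, and a later plan can name a source but cannot create data that were not collected.

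A reader might also infer that the strata are certainly invalid because they are formed after randomisation, and that comparisons between arms are therefore broken. The documents do not support this. Schools were randomised before baseline assessments, so T0 values also follow randomisation; the issue is exposure to the intervention. Secondary outcomes are examined as change within each arm with no formal between-arm testing, and cumulative incidence is compared only descriptively. No criterion in Table 7 uses the score.

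Finally, the illustrated bias is well below sampling noise. That is fair, and it limits the weight of the selection problem. It does not answer the timing problem, which is about what the strata mean.

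**Conclusion.** The point holds conditionally. The stated stratifier and the stated schedule conflict. Unless the IDEA-RS was collected in Phase 1, the strata would first be defined at T1, could not identify baseline risk, and might be selected differently by arm.

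Severity is minor to moderate. The review is descriptive and exploratory, and the progression decision does not use it. It matters because its stated purpose is targeting, and the same section says all results are meant to inform a definitive trial. The 0.8 to 3.7 point range rests entirely on the assumed shift, correlation, risk model and median split. It shows direction and rough order only, and is not an estimate for this trial.

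**What to change.** Reconcile footnote B of Table 5 with the stratification sentence, in this order of preference:

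1. If Phase 1 collected the IDEA-RS, say so and define the strata from that score.
2. Otherwise, stratify on a reduced score built only from the demographic and education items of the IDEA-RS that were collected at T0. Neither section carries the footnote, so the default schedule places both at T0.
3. If neither exists, drop the stratified review and report the IDEA-RS only as a follow-up outcome.

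The cost is one sentence and no new data collection. The drawback of the second option is that a reduced score predicts less well than the full 11 items, and this should be stated beside any result.

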#### Cost and cost consequences analyses

Cost analyses will consist of first calculating the costs of delivering the interventions in each country, both under conditions of the ALIVE study and under predicted real-world scenarios. For this, we will estimate unit costs for staff time and apply unit costs to time inputs of staff to calculate workforce costs. Similarly, we will determine market prices for other cost items such as material, travel and equipment. We will then apply unit costs and market prices to each item with the total costs of delivering the interventions in each country being aggregated. Sensitivity analysis will be conducted to reflect uncertainty of some of the parameters.

#### Qualitative analyses

Qualitative data analysis will be conducted separately in each country following procedures for inductive thematic analysis, using a qualitative analysis software (e.g. NVivo). Initial coding will be done by at least two persons with an overlap of at least 10% of the transcriptions, or until a 70% inter-rater agreement is reached. We will be using a framework analysis approach [75]. We will be combining qualitative and quantitative findings, using a convergent parallel mixed methods approach. The findings will primarily be used for revising the intervention content and delivery for a possible future effectiveness trial. Moreover, the qualitative data was used to gauge the safety of the cash transfers in the combined and economic intervention arms.

### Data management

Study information and consent forms will be kept in locked cabinets in locked offices or encrypted and password-protected computers in the case they are stored digitally. All data obtained via ODK, HRV Logger and the neuropsychological task applications will be anonymised using participant ID numbers during data collection and when exported for analysis and storage. Interviews will be pseudonymised as they are being transcribed and audio-recordings will be destroyed immediately after transcription.

Following project completion, anonymised electronic data and all metadata will be stored on King’s College London Open Research Data System (KORDS), a data repository platform which allows for long-term storage of quantitative and qualitative data; it also allows datasets to be accessible to other researchers. The data will include an embargo of 2 years, after which the quantitative data will be openly available. Qualitative data will also be stored using KORDS, but will not be publicly available, and instead shared upon request. This is due to the sensitive and context-specific nature of qualitative data.

### Dissemination

Results of the pilot cRCT will be communicated to participants and to the adolescent advisory groups in each site, as well as to other researchers through common dissemination channels. There will be no publication restrictions and links to papers published will be made available on the ALIVE website. We will use standard authorship criteria as per ICMJE.

## Discussion

The aim of the study is to test study procedures and assess the feasibility and acceptability of a new intervention combining self-regulation and economic components to prevent depression and anxiety among adolescents living in urban poverty. Given the bidirectional relationship between poverty and poor mental health, there is a need to generate evidence on the effectiveness of interventions which address both aspects simultaneously. With this study, we expect to meet criteria for progression to full trial that have been established for intervention implementation (i.e. fidelity, retention, adverse events, experience with cash transfers) and trial procedures (i.e. randomisation, masking, data collection, retention, contamination), as well as demonstrating sensitivity to change on all self-report and neuropsychological outcome measures, primarily among participants in the combined intervention arm. From this pilot trial, we will learn whether the interventions, and especially the cash transfer, had any negative impact (e.g. perceived inequity, reduced motivation), and how these can be better mitigated in a future trial. Equally we want to understand whether and how contextual factors might influence aspects of feasibility—especially given the three different study sites (e.g. levels of poverty, gender or cultural factors, across and within the Colombia, Nepal and South African samples). For any of the above findings, we will review if and what changes can be made to address any biases or improve procedures or intervention content.

On the one hand, we hypothesise that the self-regulation aspect of the intervention will provide access to a supportive peer group and environment, including caregiver support, as well as a means to build a positive self-concept by independently mastering challenging new tasks, and offer relief from the stress caused by the adversity they experience daily; all of which should promote self-regulation, as well as improve stress management, sleep and communication with caregivers, which in turn may improve hope and increase school attendance and retention, all reducing risk of developing depression or anxiety disorders. We hypothesise that the economic intervention will reduce family financial stress, increase adolescents’ sense of control and security, enhance educational opportunities, increase hope and future orientation, improve peer and family relationships, develop life skills and increase resilience to adverse environments, as well as increase caregivers’ willingness to invest in their children’s human capital and wellbeing, also reducing risk of developing depression or anxiety disorders. It may also increase the set of possible aspirations caregivers have for their children [76], which may in turn lead to larger investments in their human capital. From the adolescent perspective, financial education should empower them to make better informed decisions about the management of their finances, including the cash transfers. Similarly, negotiation training and information on education should enable the adolescents to increase the probability of strategic cooperation that may strengthen their ability to influence their parents’ decision to raise investments. This may improve education outcomes in the short- to medium-term and promote mental wellbeing among adolescents. It is thus essential to conduct a feasibility study first that combines both elements of self-regulation and anti-poverty interventions, as well as assesses the relative change between intervention arms that combine or separate these elements.

